## **9.5. Baseline Assessments**

### **Visit 1 – screening visit and screening 1.5 T MRI**

Eligibility of participants will be re-checked by pre-defined inclusion/exclusion criteria (see 6.2 and 6.3 for details) by the study team and MRI safety checks will be conducted. Written informed screening consent will be obtained by GCP trained investigators or research nurses who have also been trained to obtain consent for the study and procedures and listed on the study delegation log (20 minutes).

Anthropometric measurements such as height, weight, BMI will be recorded, and routine cardiovascular examination will afford the detection of any previously undiagnosed pathology that may have implications for safety. Participants will be asked to complete the Kansas City Cardiomyopathy Questionnaire (KCCQ) so assess baseline quality of life scores. Standard 12 lead electrocardiogram will be taken, which is a highly routine test, and baseline blood tests will be taken (approximately 16ml) (10 minutes)

A 1.5 T Cardiac Magnetic Resonance (CMR) scan will be performed on a 1.5 Tesla MR scanner at the OCMR with sequences optimised to minimise device related artefact to allow us to clearly visualise the stellate ganglia and heart. Participants will lie in a supine position and a dedicated coil will be placed around their chest, neck and head. Oxford University Hospitals NHS Foundation Trust has a standard operating procedure in place (developed with the Chief Investigator) for MR imaging of patients with implantable cardiac devices and this will be adhered to. The expected magnetic resonance imaging time is less than 60 -90 minutes. There is a scheduled 5–10-minute break during scanning.

We anticipate a 20-30% screening failure so we will not proceed with formal study consent until eligibility is confirmed following screening assessment. Patients who pass screening will be invited to formally enrol into the study and will proceed as outlined below. Patients who fail screening will exit at this point.

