#### **11.2. Description of the Statistical Methods**

To measure our primary safety endpoint, we will measure the frequency of adverse events in the 6 months post radiotherapy. Our trial is powered to detect adverse event rates of 34% (see below)

For secondary outcome measures such as changes in circulating biomarker levels (NPY) and changes in number of device therapies following radiotherapy we will use non-parametric tests such as a Wilcoxon signed rank test to determine if changes are statistically significant.

To assess correlation between changes in biomarker levels and number of device therapies we will use a correlation matrix using non-parametric correlation tests such as Spearman rank-order correlation.

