#### **11.3. Sample Size Determination**

Considering that all patients will have failed pharmacological treatments to prevent VT, the population is expected to be at particularly high risk and SAE rates  $\leq 34\%$  (as reported for surgical CSD), and efficacy rates of 50% would be clinically acceptable. To be 80% powered to demonstrate a SAE rate not

exceeding 34% (range 9-34%) on a one sided, one sample test for proportions (alpha 0.05) would require 13 patients. Considering that all patients will have failed pharmacological treatments to prevent dangerous heart rhythms, the population is expected to be at particularly high risk of further dangerous heart rhythms. Efficacy rates of 50% would be clinically acceptable. We anticipate screening at least 16 patients to allow for a 20% drop out rate, **which has been costed in our BHF grant.**

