#### **11.7. The Level of Statistical Significance**

We are 80% powered to demonstrate a SAE rate not exceeding 34% (range 9-34%) on a one sided, one sample test for proportions (alpha 0.05).

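### Thirteen patients do not give the stated 80% power to rule out a 34% SAE rate: at a true rate of 9% power is about 67%, and the 13 fits a test with the hypotheses swapped

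*Protocol*

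**What the plan says.** Section 11.3 takes 34%, the complication rate reported for surgical denervation, as the highest acceptable SAE rate. It says that 80% power to show the rate is no higher, "on a one sided, one sample test for proportions (alpha 0.05) would require 13 patients". Section 11.7 repeats this: "We are 80% powered to demonstrate a SAE rate not exceeding 34% (range 9-34%) on a one sided, one sample test for proportions". Neither section names the true rate at which the 80% applies; the only other figure is the lower end of the bracketed range, 9%. Neither gives the number of SAEs at which the claim would be met.

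Section 11.2 words the aim in the other direction: "Our trial is powered to detect adverse event rates of 34"%. Sections 7 and 10 likewise describe the study as powered to detect SAEs. Section 11.1 says no separate statistical analysis plan is in use, so section 11 is the whole plan.

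**The concern.** Demonstrating that a rate does not exceed 34% means testing the null hypothesis that it is 34% or more, and rejecting that when few events occur. Being powered to detect a rate of 34% means the opposite: rejecting a lower rate when many events occur. The two tests need different sample sizes and support different conclusions. The protocol describes both and attaches one number, 13, to them.

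At stake is the only justification given for the sample size, on the primary safety endpoint, and the reading of the final result. With no success rule written down, a reader of the results cannot tell which SAE count rules out 34%.

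**Working it through.** **Inputs.** n = 13, one-sided alpha 0.05, stated power 80% and p0 = 0.34 come from 11.3 and 11.7. p1 = 0.09 is the lower end of the range in those sections, taken here as the true rate; this is an assumption.

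**1. Trying to reproduce 13 in the stated direction (null 34%, true rate 9%).** The score formula is n = [(z_a·√(p0·q0) + z_b·√(p1·q1)) / (p0 − p1)]², where q = 1 − p.

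- √(0.34 × 0.66) = 0.4737 and √(0.09 × 0.91) = 0.2862
- n = [(1.645 × 0.4737 + 0.842 × 0.2862) / 0.25]² = 16.6, so 17
- Power at n = 13: Φ[(0.25·√13 − 1.645 × 0.4737) / 0.2862] = 66.5%

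Other one-sided formulas do not give 13 either:

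| Formula | n for 80% power |
|---|---|
| Arcsine | 16 (74.1% power at n = 13) |
| Score, continuity-corrected | 19 to 21 |
| Variance under the null | 23 |
| Wald, variance at 9% | 9 |

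**2. Exact binomial test at n = 13.**

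| SAEs allowed | Type I error at 34% | Power at 9% |
|---|---|---|
| 0 | 0.5% | 29.3% |
| at most 1 | 3.5% | 67.1% |
| at most 2 | 12.8% | 89.5% |

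Only the first two rows respect alpha 0.05, so the rule is at most 1 SAE and power is 67.1%. The score test gives the same cut-off: z = −2.00 with 1 SAE and −1.42 with 2, against −1.645. A Wald test would also pass 2 SAEs (z = −1.86), but that rule's true type I error is 12.8%. No cut-off at n = 13 meets both stated figures.

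**3. Sensitivity to the assumed true rate, with at most 1 SAE in 13.**

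| True rate | 5% | 6% | 7% | 9% | 10% | 15% |
|---|---|---|---|---|---|---|
| Power | 86% | 82% | 77% | 67% | 62% | 40% |

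At 6.4%: 0.936¹³ + 13 × 0.064 × 0.936¹² = 0.423 + 0.376 = 0.80. Every rate within 9–34% gives 67% or less.

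**4. Where 13 may come from.** Swapping the hypotheses (null 9%, alternative 34%) in the same formula gives [(1.645 × 0.2862 + 0.842 × 0.4737) / 0.25]² = 12.1, so 13, with 81.8% power by the approximation. The exact test in that direction rejects with 4 or more SAEs (alpha 2.4%) and has 69.6% power.

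**5. What the observed counts would support.** The one-sided 95% exact upper bounds are 31.6% for 1 of 13, 41.0% for 2 of 13 and 49.5% for 3 of 13.

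**6. For scale.** The smallest n with exact power of at least 80% at 9% is 17 (at most 2 SAEs, alpha 3.9%, power 80.7%).

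**The case against.** The strongest reply is that 9% is never named as the design alternative. That stands, and 67% must be read as conditional on it. It does not rescue the 80%, which needs a true rate of about 6.4%, outside the protocol's own range.

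A second reply is that this is a small case series. Section 11.2 plans only to measure the frequency of events, and escalation and stopping rest on SAE counts and committee review. That stands as a limit on the consequences: no dosing or stopping decision depends on the power figure. The protocol nevertheless makes the power claim itself.

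Three stronger readings are tempting, and the documents do not support them:

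- A reader might blame the shortfall on the coarse steps of an exact test with 13 patients. The continuous score approximation is just as short (66.5%), so the direction of the hypotheses is the likelier explanation.
- A reader might infer that 2 or 3 SAEs in 13 would be reported as showing a rate below 34%. The protocol says nothing of the kind; it simply gives no rule.
- A reader might add that the screening target of 16 is also wrong, since 13/0.8 = 16.25 and section 9.5 says "We anticipate a 20-30% screening failure". But 16 is given as a minimum, the difference is immaterial, withdrawals are replaced until 13 complete, and the 20% drop-out may overlap with screening failure.

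**Conclusion.** The power statement in 11.3 and 11.7 is wrong as written. For the test those sections describe, and with 9% as the true rate, the chance of missing the conclusion is 33% rather than 20%. The calculation also assumes one common SAE rate across the dose levels and exactly 13 analysed participants.

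The swapped-hypothesis explanation is an inference from matching numbers and wording, because the protocol does not show its calculation. It would not justify the claim in any case: failing to reject 9% does not demonstrate a rate below 34%, and the exact power of that test is also under 80%.

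The finding does not show that 13 is too few for a dose-escalation series. It shows that the stated statistical justification for 13 does not hold.

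**What to change.** - **Sections 11.3 and 11.7:** state the null (34%), the assumed true rate, the success rule (at most 1 of 13 analysed participants with a primary-endpoint SAE, attained alpha 3.5%) and the power (67% at 9%; 80% at about 6.4%). Note that this assumes one common SAE rate across dose levels.
- **Section 11.2, section 7 and the opening of section 10:** bring the wording about being powered to detect events into line with that hypothesis.
- **Section 11.2:** report the SAE proportion with its exact confidence interval.
- **Section 11.4:** make the denominator of the rule consistent with the analysis population. Section 11.4 counts only participants who completed bilateral radiotherapy, while section 7 gives no further fractions to a patient who has an SAE. The text must say whether such a patient is among the 13.

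The cost is text only, with no extra enrolment. The downside is a less favourable stated power.

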#### **11.4. Analysis populations**

All participants who completed their course of radiotherapy bilaterally to the stellate ganglia (an adverse event analysis).

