A dose escalation protocol will be used to determine the lowest radiotherapy dose that can safely achieve sympathetic downregulation. This protocol will involve 13 patients with the doses escalated as follows: The first 3 patients would be treated at 8 Gy per fraction for 3 fractions on alternate days. If no serious adverse events occur then we will increase the dose to 9 Gy per fraction for 3 fractions on alternate days in the next 3 patients, 10 Gy per fraction for the next 3 patients for 3 fractions on alternate days and 11 Gy per fraction for 3 fractions on alternate days for the final 4 patients (figure 2). There will be a minimum of 6 weeks between the last participant treated at each dose before escalation the next dose to allow for detection of adverse events at participants' 6 week follow up visit. Before each dose escalation we will have an independent safety committee review all patient data and radiotherapy doses will only be escalated if there are no safety concerns.

Our study is a safety study, and we are powered to detect serious adverse events as our primary endpoint. Serious adverse events (SAEs) defined as any related and unexpected grade 3 toxicity requiring hospitalization, grade 4 toxicity or grade 5 toxicity as defined by the common terminology criteria for adverse events.

If a serious adverse event occurs, then no further fractions would be given to that patient and the dose would be reduced by 1 Gy for all subsequent patients (up to a total of 13 patients) without further dose escalation. If an SAE occurs at the lowest radiotherapy dose (8 Gy per fraction for 3 fractions) all subsequent patients will receive treatment at the even lower dose of 7 Gy per fraction for 3 fractions, if approved by our independent safety committee. However as highlighted in section 5 we have chosen a starting dose within the safe upper limit for neuronal tissue, so we do not anticipate this. An early stopping rule will be set to halt enrolment if 4 out of the first 8 patients develop and SAE. If patients withdraw from this trial then they will be replaced, and the study will continue until 13 patients have completed the dose escalation protocol (as detailed in section 9.8). We will not recruit any extra participants into our dose escalation protocol, unless participants withdraw, in which case they will be replaced. Once 13 participants complete the dose escalation protocol no further patients will be recruited.

Figure 2.

[figure not shown]

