### **9.8. Early Discontinuation/Withdrawal of Participants**

During the course of the study a participant may choose to withdraw early from the study treatment at any time. This may happen for several reasons, including but not limited to:

- The occurrence of what the participant perceives as an intolerable AE.
- Inability to comply with study procedures
- Participant decision

Participants may choose to stop treatment and/or study assessments but may remain on study follow-up.

Participants may also withdraw their consent, meaning that they wish to withdraw from the study completely.

According to the design of the study, participants may have the following three options for withdrawal;

- 1) Participants may withdraw from active follow-up and further communication but allow the study team to continue to access their medical records and any relevant hospital data that is recorded as part of routine standard of care; i.e., Remote monitoring of their ICD.
- 2) Participants can withdraw from the study but permit data and samples obtained up until the point of withdrawal to be retained for use in the study analysis. No further data or samples would be collected after withdrawal.
- 3) Participants can withdraw completely from the study and withdraw the data and samples collected up until the point of withdrawal. The data and samples already collected would not be used in the final study analysis. A limitation to this withdrawal would be any data that has already been used as part of interim analysis, including by the independent safety committee.

In addition, the Investigator may discontinue a participant from the study treatment at any time if the Investigator considers it necessary for any reason including, but not limited to:

- Pregnancy
- Ineligibility (either arising during the study or retrospectively having been overlooked at screening)
- Significant protocol deviation
- Significant non-compliance with treatment regimen or study requirements
- Clinical decision

The type of withdrawal and reason for withdrawal will be recorded in the CRF.

Withdrawn participants will be replaced

Patients who have withdrawn from the study who also opt out of further study follow up will continue to be followed indefinitely up as part of their routine clinical care. This will include follow up under the device clinic, and where applicable by the heart failure and arrhythmia service.

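### The analysis set, the replacement rule and the 6-month endpoint are not reconciled, so a participant who withdraws after radiotherapy can be replaced and still sit in the denominator with partial follow-up

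*Protocol*

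**What the plan says.** - **Analysis set (11.4).** "All participants who completed their course of radiotherapy bilaterally to the stellate ganglia (an adverse event analysis"). Completing the course is the only condition.
- **Primary measure (11.2).** "we will measure the frequency of adverse events in the 6 months post radiotherapy". No estimator and no rule for incomplete follow-up is given. Sections 3 and 6 also place the primary SAE endpoint in the first 6 months.
- **Replacement (9.8).** "Withdrawn participants will be replaced", with no limit on when the withdrawal happens.
- **End of recruitment (7).** "the study will continue until 13 patients have completed the dose escalation protocol". Completion is not defined: it could mean the three fractions, or the fractions plus 6 months.
- **Withdrawal routes (9.8).** Option 1 ends active visits but leaves medical records and ICD monitoring open to the team. Option 2 keeps data up to withdrawal and collects nothing later. Option 3 takes the participant's data out of the final analysis.
- **Test (11.3).** The comparison with 34% is based "on a one sided, one sample test for proportions (alpha 0.05) would require 13 patients".
- **Dropout (11.3).** "We anticipate screening at least 16 patients to allow for a 20% drop out rate".
- **Separate SAP (11.1).** The protocol says that none is in use, so section 11 is the whole plan.

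**The concern.** A 6-month event proportion needs either 6 months of observation on everyone in the denominator or a method that allows for shorter observation. Section 11.4 requires neither. Someone who receives all fractions and leaves under option 2 meets the 11.4 definition and is also replaced under 9.8. If the rate is then taken as a count over N, that person adds a full unit to the denominator but only part of a 6-month risk to the numerator.

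The error runs towards a favourable safety result, in a study where one or two events can decide the conclusion. For example, 5 SAEs are 5/13 = 38.5% of the planned number but 5/15 = 33.3% if two such leavers are added. The first figure is above the 34% benchmark and the second is below it.

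**Working it through.** **1. The plan's own figure.** Inputs from 11.3: rates 9% and 34%, one-sided alpha 0.05, power 80%. The one-sample formula is n = [(z_a√(p0q0) + z_b√(p1q1)) / (p1 − p0)]².
- With p0 = 9% and p1 = 34%: [(1.645 × 0.286 + 0.842 × 0.474) / 0.25]² = 12.09, so 13. This reproduces the stated number.
- With p0 = 34% and p1 = 9%, the direction worded in 11.3 and 11.7: 16.65, so 17.

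The direction of the test is a separate matter. What counts here is that 13 has no allowance for a denominator that grows through replacement.

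**2. Who can be replaced and retained.** Take a participant who completes all fractions and withdraws before month 6.

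| Route | In the 11.4 set? | Replaced under 9.8? | Follow-up to month 6 |
|---|---|---|---|
| Option 1 | Yes | Yes | Obtainable from records, though not required |
| Option 2 | Yes | Yes | None after withdrawal |
| Option 3 | No, data removed | Yes | Not relevant |

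Only option 2 necessarily leaves partial follow-up in the denominator.

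**3. Effect on a crude rate.** Assumptions, none of them in the protocol: 13 participants followed in full, L option-2 leavers who are each replaced, leavers with the same underlying risk, constant hazard, and a fraction f of the 6 months observed before leaving. With true 6-month risk p = 0.34, a leaver's observed risk is 1 − 0.66^f: 0 at f = 0, 0.099 at f = 0.25 and 0.188 at f = 0.5.

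Expected crude rate = [13 × 0.34 + L(1 − 0.66^f)] / (13 + L), where 13 × 0.34 = 4.42.
- L = 1: 4.42/14 = 31.6% (f = 0) to 4.608/14 = 32.9% (f = 0.5).
- L = 3: 4.42/16 = 27.6% (f = 0), 4.716/16 = 29.5% (f = 0.25), 4.983/16 = 31.1% (f = 0.5).

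**4. Effect on a test against 34%.** The protocol does not say whether the test is exact or approximate, and it states no critical count.
- *Exact binomial:* the largest count with P(X ≤ k) ≤ 0.05 at 34% is k = 1 for every N from 13 to 16. The chance of passing at a true 34% is 3.5% at N = 13 and does not rise with up to three leavers.
- *Score test:* k is the whole-number part of 0.34N − 1.645√(N × 0.34 × 0.66). This gives 1.61 at N = 13, 1.84 at N = 14, 2.08 at N = 15 and 2.32 at N = 16. The cutoff therefore moves from 1 to 2 SAEs at N = 15. With two leavers, the chance of passing at a true 34% is 12.8% (f = 0) to 9.5% (f = 0.5). It would be 7.2% with 15 participants followed in full, so part of the excess belongs to the approximation itself.

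**The case against.** Several readings go further than the text allows.

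- *Unobserved time is counted as SAE-free.* A reader might infer this, but no section says it. It follows only if the 6-month frequency in 11.2 is a crude proportion. The one-proportion test in 11.3 points that way, but the estimator is not named.
- *Every post-treatment withdrawal dilutes the rate.* This does not follow. Under option 1, hospital records would largely show toxicity that led to hospitalisation, was life-threatening or was fatal. Option 3 takes the person out of the denominator.
- *Replacement together with retention is certain.* It depends on section 7. If completion there means radiotherapy only, the leaver is already one of the 13, which conflicts with 9.8. The passages need reconciling on either reading.
- *The protocol's 20% is the loss to expect after treatment.* Sections 8.1 and 11.3 attach it to 16 patients screened, and 9.3 and 9.5 expect 20-30% screening failure. It is no estimate of loss after radiotherapy.
- *Leavers are selected because they had toxicity.* The intolerable-event reason in 9.8 concerns withdrawal from study treatment, and 10.5 keeps participants with an SAE under follow-up. Informative loss is possible but not shown.
- *Constant hazard.* Section 10 expects dose-limiting toxicity within 6 weeks. If risk falls early, later leavers dilute less than shown.

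These objections narrow the point. They do not remove the gap for option-2 leavers, which no other document fills. A denominator above 13 is also not harmful in itself; the bias needs lost follow-up.

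**Conclusion.** The concern holds in a limited form. Sections 7, 9.8, 11.2 and 11.4 do not fit together. An option-2 leaver after radiotherapy can be replaced and still counted with partial follow-up, so N can exceed 13 and a crude 6-month SAE rate can be too low. On the assumption of 1 to 3 such leavers, who depart somewhere between the end of treatment and halfway through follow-up, the expected understatement at a true 34% is about 1 to 6 percentage points.

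A reader might infer that the trial's type I error is inflated. The documents do not support that as a general statement. With an exact test nothing changes up to N = 16; with a score test the cutoff shifts once there are two leavers. With no leavers of this kind, there is no bias.

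**What to change.** 1. **Section 7:** define what completing the dose escalation protocol means (radiotherapy only, or radiotherapy plus 6 months) and reconcile it with the replacement rule in 9.8.
2. **Sections 11.2 and 11.4:** estimate the 6-month SAE rate over all irradiated participants, replaced or not, as a cumulative incidence that uses each person's observed time, with unrelated death as a competing event. State how the comparison with 34% uses this estimate. Basing it on all irradiated participants also brings in those whose course ends early after an SAE (sections 7 and 9.6), whom the 11.4 wording would leave out.
3. **Option-1 withdrawals:** obtain SAE status to month 6 from the records that remain accessible.
4. **Sensitivity analysis:** count participants lost before month 6 as SAEs, labelled as a worst case.

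Scoring only those who had an SAE or were followed for the full 6 months is not a good substitute. It keeps early leavers only when they had an event. With three leavers at halfway and a true 34%, it would give about (4.42 + 0.56)/(13 + 0.56) = 36.7%. A fixed maximum number of SAEs is not proposed either, since the protocol states none.

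The cost is a few sentences and a records check that option 1 already permits. The reported rate may be slightly less favourable and its interval slightly wider. The cumulative incidence still assumes that leaving is unrelated to SAE risk, which is why the worst-case analysis is needed beside it.

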### Visits 4 to 6 – Hypofractionated radiotherapy to the stellate ganglia

Over the course of one-week, patients will undergo up to 3 fractions of hypofractionated radiotherapy targeted bilaterally to the lower half of the stellate ganglia and T1-2 paravertebral chain (60 minutes).

Prior to each fraction of radiotherapy blood samples (approximately 16 ml) will be taken to monitor plasma levels of NPY and other biomarkers. Routine blood tests (including renal function, full blood count and thyroid function) will also be checked prior to the first fraction of treatment. Blood samples will be labelled with the participants' study number and stored for analysis. All stored samples will be de-identified and will only be identified by a study specific participant number and will be destroyed after processing, unless participants have specifically consented to have their samples stored for use in future studies (10 minutes)

Before and after each fraction of radiotherapy a cardiovascular examination and neurological examination will be performed by one of the study doctors paying attention to signs of Horner's syndrome

(ptosis and pupil constriction) or upper limb sensory impairment. Cardiovascular observations including postural blood pressures and heart rate will be recorded, and an electrocardiogram will be performed. New postural hypotension defined as a symptomatic postural blood pressure drop of 20mmHg will be considered significant. (10 minutes each) If any serious treatment related adverse events are detected, then no further fractions of radiation will be delivered to that patient.

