## **10. SAFETY REPORTING**

This study is primarily a safety study and is specifically powered to detect SAEs (see section 11.3). The safety reporting window will be from the first fraction of radiotherapy until completion of the 6 months study follow up. A 6 months SAE reporting window is felt to be sufficient as adverse events related to cardiac sympathetic denervation should be apparent during treatment or within days, weeks or months of completion of radiotherapy if we consider trigeminal neuralgia as a parallel (78). Indeed, over the course of 6 months we will monitor any adverse events and side-effects and the expectation is that side effects will improve rather than worsen over this time period, as is observed following surgical removal of the stellate ganglia(20)

With respect to adverse events following radiotherapy, we expect to detect any dose limiting toxicity within 6 weeks of completion of radiotherapy, which is an accepted monitoring period for dose escalation trials involving radiotherapy (79). In terms of stochastic adverse effects, in the long term, ionising radiation can also cause cancer which manifests itself after many years or decades and is an accepted side-effect of the treatment. It is not likely that we would detect such adverse events even if our reporting window was extended beyond 6 months. Indeed, our study population of patients with severe heart failure and recurrent ventricular arrhythmias has a particularly poor prognosis, even despite all current available medical therapies, with mortality rates observed in excess of 50% at 5 years(67). As such late stochastic events might never become apparent.

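### The adverse event analysis is limited to participants who completed radiotherapy, so a patient whose SAE stops treatment is left out of the primary SAE rate, which is biased downward

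*Protocol*

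**What the plan says.** - **Analysis set.** Protocol section 11.4 gives a single population: "All participants who completed their course of radiotherapy bilaterally to the stellate ganglia (an adverse event analysis". Section 11.1 states that no separate SAP is in use, so this is the operative rule.
- **Effect of an SAE on treatment.** Section 7: "If a serious adverse event occurs, then no further fractions would be given to that patient". Section 9.6 (visits 4 to 6) repeats it: "If any serious treatment related adverse events are detected, then no further fractions of radiation will be delivered to that patient".
- **When the endpoint is assessed.** The table in section 6 includes all radiotherapy sessions as well as the monitoring visits. Section 10: "The safety reporting window will be from the first fraction of radiotherapy until completion of the 6 months study follow up". Section 11.2 words it differently: "we will measure the frequency of adverse events in the 6 months post radiotherapy".
- **Replacement.** Section 7 replaces patients who withdraw and says "the study will continue until 13 patients have completed the dose escalation protocol". Section 9.8 lists among the reasons for withdrawing early "The occurrence of what the participant perceives as an intolerable AE", also covers discontinuation of treatment by the investigator, and states: "Withdrawn participants will be replaced".
- **Follow-up.** Section 9.8 lets a participant stop treatment but stay in follow-up. Section 10.5 keeps participants with an SAE under follow-up for the rest of the study.

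**The concern.** The primary endpoint helps to decide who is analysed for it. An SAE after fraction 1 or 2 ends treatment, ending treatment makes the patient a non-completer, and non-completers are outside the only set defined. Such a patient leaves both numerator and denominator. By the same rule, a fatal toxicity between fractions would fall outside the analysis.

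Section 9.4.1 presents staged delivery over three fractions as a way to detect complications early, so events between fractions are among those the design sets out to find. In a trial whose main purpose is safety, and which compares its SAE rate with a 34% reference from surgical denervation, losing even one such event can change the conclusion.

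**Working it through.** **The plan's own figure.** Section 11.3 states 13 patients for a one-sided one-sample test of proportions, alpha 0.05, power 80%, rates 9% and 34%. With the normal approximation,

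n = [1.645·√(p0(1−p0)) + 0.842·√(p1(1−p1))]² / (p1−p0)²

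- p0 = 0.09, p1 = 0.34: n = 12.09, so 13. This reproduces the stated figure.
- p0 = 0.34, p1 = 0.09 (the direction in the text, showing a rate not above 34%): n = 16.65, so 17. This does not reproduce it.

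The protocol gives no decision rule for the final count. I therefore assume the exact 5% rule for the direction in the text. With 13 patients and a true rate of 34%, P(X ≤ 2) = 0.128 and P(X ≤ 1) = 0.035, so at most 1 SAE in 13 would be needed.

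**Effect on the rate.** Let p be the true SAE rate in treated patients and f the share of SAEs arising before the last fraction. Completers are the fraction 1 − pf of those treated, and those among them with an SAE are p(1−f). The completer rate is

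q = p(1−f) / (1−pf)

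The protocol does not give f, so a range is shown. The rate is assumed constant across doses.

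| f | q at p = 0.34 | P(X ≤ 1 of 13) |
|---|---|---|
| 0 | 34.0% | 3.5% |
| 10% | 0.306/0.966 = 31.7% | 5.0% |
| 25% | 0.255/0.915 = 27.9% | 8.6% |
| 50% | 0.170/0.830 = 20.5% | 22% |
| 75% | 0.085/0.745 = 11.4% | 55% |

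With all treated patients in the denominator, the estimated rate is p for every f.

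If the test is instead read in the direction that yields 13 (null 9%), the exact rule is at least 4 SAEs in 13. Its power at a true 34% falls from 69.6% (f = 0) to 51.1% (f = 25%) and 26.8% (f = 50%). Detection is weakened under either reading.

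**One patient.** Suppose 2 SAEs, one of which stopped treatment. Exact one-sided p-values are against 34%.

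| Set | Without replacement | With one replacement |
|---|---|---|
| All treated | 2/13 = 15.4%, p = 0.128 | 2/14 = 14.3%, p = 0.096 |
| Completers | 1/12 = 8.3%, p = 0.049 | 1/13 = 7.7%, p = 0.035 |

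Excluding one harmed patient moves the result across 0.05 with or without replacement.

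**Section 11.2.** Its wording counts events after radiotherapy, against sections 6 and 10. For SAEs this adds little, because a patient with an SAE before the last fraction is already out as a non-completer. It matters mainly for non-serious side effects during the treatment week.

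**The case against.** - **Few SAEs may fall before the last fraction.** Three alternate-day fractions span about 4 days, against 6 months of follow-up. A flat hazard (an illustration only) gives f of about 4/(4+182) = 2% and a completer rate of 0.3332/0.9932 = 33.5%. Section 10 expects dose-limiting toxicity within 6 weeks of completion. This stands as a limit on size: the larger figures need half or more of all SAEs to arise within days, and nothing in the protocol supports a particular value. It does not change the direction.
- **Replacement.** A reader might infer that patients stopped for an SAE are withdrawn and replaced. The protocol does not say so. Replacement applies to those who withdraw, section 9.8 separates stopping treatment from leaving follow-up, and section 10.5 keeps SAE patients in follow-up. Sections 7 and 9.8 allow replacement, and it would hide the loss further, but the bias does not need it.
- **Oversight.** A reader might also infer that a toxic treatment could pass unnoticed. The documents do not support that. The committee reviews all patient data before each escalation, an SAE found at follow-up triggers a review and a pause, and the rule of 4 or more SAEs in the first 8 counts participants, not completers.
- **The model is simple.** An SAE lowers the dose for later patients and enrolment can stop early, so a constant 34% over 13 patients is a simplification.
- **Completion could mean the course as delivered.** Section 9.6 speaks of up to 3 fractions. Section 11.4 does not say this, and sections 7 and 9.4.1 describe a three-fraction course. If that was the intent, it still needs stating.

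**Conclusion.** The point holds. As written, section 11.4 excludes from the primary SAE rate any patient whose SAE occurs before the last fraction. It contradicts sections 6 and 10, and no separate SAP exists to repair it. The direction of the bias is certain on the plain reading. The size is not: at a true 34% the completer rate runs from 34% (f = 0) to 11.4% (f = 75%), and the chance of a result that would appear to show a rate below 34% runs from 3.5% to 55%. These figures assume a value of f, a constant rate across doses and a decision rule that the protocol does not state. The one-patient example needs no value of f; only its p-values rest on the assumed test. The defect is confined to the final reported rate, which could then disagree with what the safety committee saw.

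**What to change.** 1. In section 11.4, define the primary safety population as every participant who received any part of any fraction, with events counted from the first fraction to 6 months.
2. Reword section 11.2 to the same window, consistent with sections 6 and 10.
3. State in sections 7 and 9.8 that treated participants who stop, or who are replaced, stay in the numerator and denominator. The exception is a participant who withdraws data already collected under option 3 of section 9.8. Report the number of such cases and add a sensitivity analysis for them.
4. Keep the completer set as supplementary only.

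This changes wording alone and leaves the dose and treatment-stopping rules as they are. The required number of patients does not change. The cost is that the denominator may exceed 13 (if stopped patients are replaced at a true 34%, about 13/(1 − 0.34 × 0.25) = 14.2 treated on average for f = 25%) and that the reported SAE rate may be less favourable.
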